**Fig. 4 Fig4:**
[figure not shown]
Quantitative assessment of myocardial blood flow (MBF) using dynamic stress computed tomography perfusion (CTP). Short-axis MBF map obtained from dynamic stress CTP, with segmental regions of interest (ROIs) placed according to the American Heart Association 17-segment model

### Qualitative image quality assessment

All CCTA and dynamic stress CTP datasets will be independently reviewed by two board-certified cardiovascular radiologists with more than 10 years of experience who are blinded to clinical information and contrast-group assignments. Coronary image quality will be assessed on axial, multiplanar, and curved planar reformation images using a 5-point scale: 5, excellent visualization without relevant artifact; 4, good visualization with minor artifact; 3, adequate visualization with moderate artifact but diagnostic; 2, poor visualization with severe artifact and limited diagnostic confidence; and 1, nondiagnostic image quality. Volume-rendered images will be reviewed as supplementary overview images for global coronary visualization, distal vessel/side-branch conspicuity, and overall diagnostic confidence, but will not be used alone for stenosis assessment. Dynamic stress CTP interpretability will be graded using an analogous 5-point scale. Readers will also record diagnostic acceptability (acceptable vs. nonacceptable) and diagnostic confidence (high, medium, or low). Discrepancies will be resolved by consensus after independent review.

### Exploratory diagnostic performance analyses: ICA and FFR

Exploratory diagnostic performance analyses will be performed in participants who undergo ICA and/or FFR as part of routine clinical care. The decision to perform CCTA with dynamic stress CTP, as well as subsequent ICA with or without FFR, will be made by the treating cardiologists according to routine clinical care and will not be dictated by study participation. Accordingly, the primary purpose of this trial is to compare contrast media protocols for CCTA enhancement and quantitative dynamic stress CTP assessment, rather than to establish diagnostic validity of CCTA or CTP.

ICA will be interpreted by experienced interventional cardiologists. Anatomic stenosis severity will be recorded per vessel using standard quantitative or visual assessment; ≥ 50% luminal narrowing will define significant stenosis for exploratory CCTA diagnostic performance analyses. For physiology, when FFR is measured, FFR ≤ 0.80 will define functionally significant ischemia in the interrogated vessel. For CCTA diagnostic performance analyses, CCTA-derived stenosis categories will be compared with ICA on a per-vessel and per-patient basis. For dynamic stress CTP diagnostic performance analyses, CTP ischemia (territorial/segmental defects or low MBF) will be compared with vessel-level FFR where available, with mapping of myocardial territories to corresponding coronary vessels using standardized AHA territorial assignments and clinical correlation. Because invasive testing is clinically indicated rather than protocol mandated for all participants, these analyses are subject to potential verification bias and will be interpreted cautiously as prespecified exploratory and hypothesis-generating analyses.

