### Population and setting

The trial plans to enroll 258 adults with known or suspected CAD referred for clinically indicated cardiac CT, including CCTA with planned dynamic stress CTP. Eligible participants will be ≥ 40 years of age, will have electrocardiography (ECG)-gated imaging feasibility, and will have adequate renal function (e.g., estimated glomerular filtration rate [eGFR] ≥ 45 mL/min/1.73 m^2^). Exclusion criteria will include suspected acute myocardial infarction or unstable angina; complex congenital heart disease; significant renal dysfunction or acute kidney injury (e.g., serum creatinine ≥ 1.5 mg/dL or eGFR < 45 mL/min/1.73 m^2^); history of coronary artery bypass grafting (percutaneous coronary intervention/stents permitted and recorded); pregnancy or lactation; history of severe hypersensitivity to iodinated contrast media or vasodilator stress agents; contraindications to nitroglycerin; contraindications to adenosine triphosphate; and uncontrolled arrhythmia precluding diagnostic acquisition. Eligible participants will be recruited from the routine clinical cardiac CT population at our institution during the planned study period.

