### Patient preparation and stress protocol

Participants will be instructed to abstain from caffeine for 24 h prior to imaging and to withhold theophylline on the day of the examination. In the absence of contraindications, sublingual nitroglycerin will be administered immediately before CCTA to promote coronary vasodilation. For heart rate control, if baseline heart rate is ≥ 60/min, oral ivabradine (5 mg or 7.5 mg) will be administered per protocol. Heart rate will be measured every 10 min for 40 min; scanning will typically commence at approximately 60 min once adequate rate reduction is achieved. Dynamic stress CTP will be performed during intravenous adenosine triphosphate infusion at 140 μg/kg/min for 3 min.

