### CT acquisition protocol

All examinations will be performed on a third-generation dual-source CT scanner (SOMATOM Force, Siemens Healthineers) and will comprise coronary calcium scoring, dynamic stress CTP, and CCTA (Fig. 2). For dynamic stress CTP, acquisition will begin 4 s after contrast initiation and proceed in shuttle mode (z-axis coverage 105 mm) over a fixed 32-s interval, yielding approximately 10 to 15 time frames depending on heart rate. Images will be acquired in end-systole using collimation of 96× 0.6 mm and rotation time of 250 ms. Tube voltage will be selected using automatic tube-voltage selection (CARE kV, Siemens Healthineers), and tube current will be modulated using CARE Dose4D (Siemens Healthineers), according to the same institutional cardiac CT protocol in both contrast groups. Physiologic data, including baseline heart rate, peak heart rate during CTP, and heart rate increment, will be recorded prospectively.

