**Fig. 3 Fig3:**
[figure not shown]
Quantitative assessment of coronary computed tomography angiography (CCTA) image quality. **A**–**C** Curved multiplanar reformations of the right coronary artery (RCA), left anterior descending artery (LAD), and left circumflex artery (LCX), showing regions of interest (ROIs) placed in the proximal and distal coronary segments for attenuation measurement. **D** Ascending aortic ROI used for image noise measurement. **E** Septal myocardial ROI used for myocardial attenuation measurement. HU, Hounsfield units

Dynamic stress CTP-derived MBF will be quantified on voxel-wise MBF maps. For segmental analysis, ROIs will be drawn on short-axis MBF maps using the AHA 17-segment model, positioned ≥ 2 mm from endocardial and epicardial borders (Fig. 4). To avoid circularity, MBF thresholds will not be used to define the main MBF analysis set. The main analysis will include all analyzable myocardial segments, with sensitivity analyses in visually nonischemic segments and, when available, territories not supplied by vessels with significant anatomic stenosis or FFR-defined ischemia.

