Exploratory diagnostic performance analyses will be conducted in the subset undergoing ICA and/or FFR. For CCTA using ICA as the reference standard, sensitivity, specificity, positive predictive value, and negative predictive value will be calculated for the detection of ≥ 50% coronary artery stenosis. Overall diagnostic performance will be quantified using receiver operating characteristic (ROC) curve analysis and the area under the ROC curve (AUC). For dynamic stress CTP versus FFR, similar metrics will be calculated for detecting FFR-defined ischemia (≤ 0.80). Because multiple vessels may be contributed by a single participant, analyses will account for within-patient clustering using methods such as generalized estimating equations for binary endpoints and cluster-robust variance estimators for AUC and confidence intervals. Prespecified sensitivity analyses will evaluate the impact of verification bias, as feasible given sample size. Missing data will be described and handled using appropriate methods for the endpoint, including mixed models under missing-at-random assumptions with sensitivity analyses if missingness is substantial.

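### Stress-only CTP cannot separate old scar from ischemia, so in the exploratory comparison with FFR a scar behind a vessel with FFR above 0.80 counts as a CTP false positive

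*Protocol article*

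**What the plan says.** All references are to the protocol article.

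- **Index test** (Exploratory diagnostic performance analyses: ICA and FFR): "CTP ischemia (territorial/segmental defects or low MBF) will be compared with vessel-level FFR where available". The definition has no reversibility condition, no category for scar and no MBF cut-off.
- **Reference standard** (same section): "FFR ≤ 0.80 will define functionally significant ischemia in the interrogated vessel".
- **Metrics** (Statistical methods): "For dynamic stress CTP versus FFR, similar metrics will be calculated for detecting FFR-defined ischemia (≤ 0.80"). The set named just before this, for CCTA against ICA, is sensitivity, specificity, both predictive values and the AUC.
- **Acquisition** (CT acquisition protocol): examinations "will comprise coronary calcium scoring, dynamic stress CTP, and CCTA". Patient preparation and stress protocol adds: "Dynamic stress CTP will be performed during intravenous adenosine triphosphate infusion at 140 μg/kg/min for 3 min". No rest perfusion or delayed scan is described.
- **Population** (Population and setting): "The trial plans to enroll 258 adults with known or suspected CAD referred for clinically indicated cardiac CT". On infarction: "Exclusion criteria will include suspected acute myocardial infarction or unstable angina". Bypass surgery is excluded; earlier PCI or stenting is allowed and recorded. Old infarction is not listed.
- **Reading** (Qualitative image quality assessment): the two radiologists who review all CCTA and CTP datasets do not see clinical information.
- **MBF sensitivity sets** (Image analysis): one set is the visually nonischemic segments. The other, where the data exist, is "territories not supplied by vessels with significant anatomic stenosis or FFR-defined ischemia". The main MBF analysis uses every analyzable segment.

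**The concern.** FFR asks whether an artery limits flow. Stress CTP shows flow in the myocardium. Where myocardium is scarred and its artery has been reopened, the two can disagree while both are right: the territory shows a defect or low MBF, and FFR is above 0.80. The printed rule calls the CTP finding ischemia and the pair becomes a false positive.

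What is at stake is how the exploratory CTP figures are read. Specificity and PPV against FFR would partly reflect how many old infarcts are in the invasive subset. The article's caution names only verification bias, which is a different mechanism: scar would be misclassified even if every participant had FFR. The vessel-defined MBF sensitivity set has the same gap, because a scarred territory behind an unobstructed artery meets its definition.

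**Working it through.** The plan states no CTP specificity, infarct share or size of the FFR subset, so there is no figure to reproduce. The check is to follow one case through the text and then show the arithmetic under labelled assumptions.

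**Following one case.** Take a participant with an old infarct whose artery was later stented.

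1. Eligible? Yes: known CAD is admitted, stents are permitted, and the infarction exclusion covers suspected acute events only.
2. Can the examination separate scar from ischemia? Not with what is described. Perfusion is acquired at stress only. The CCTA about 10 minutes later is a contrast acquisition without stress, but it is given no role as a rest perfusion reference.
3. Can the readers discount the defect from the history? No, they are blinded to it.
4. Does the mention of clinical correlation help? It concerns the assignment of territories to vessels, not the separation of scar from ischemia.
5. CTP result: a defect or low MBF, hence positive.
6. FFR above 0.80: reference-negative.
7. Score: a false positive. In FFR-negative vessels this moves a count from true negative to false positive, so specificity falls. True positives are unchanged while false positives rise, so PPV falls.

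**The MBF sets.** The same territory has no significant stenosis and no FFR-defined ischemia, so it stays in the vessel-defined set. If the scar is seen as a defect, the visually nonischemic set would largely drop it. The gap therefore lies mainly in the vessel-defined set.

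**Illustration (every input is assumed; none is in the document).** Let s be the share of FFR-negative vessels that supply an infarct, d the chance that such a territory shows a defect or low MBF, and 0.80 the specificity in vessels without infarct.

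Apparent specificity = (1 − s) × 0.80 + s × (1 − d)

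| s | d | Calculation | Specificity |
|---|---|---|---|
| 0 | any | 1 × 0.80 | 80% |
| 0.05 | 0.6 | 0.95 × 0.80 + 0.05 × 0.4 | 78% |
| 0.10 | 0.8 | 0.90 × 0.80 + 0.10 × 0.2 | 74% |
| 0.20 | 0.9 | 0.80 × 0.80 + 0.20 × 0.1 | 66% |

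If infarct territories that do not show the scar can still be read as positive for other reasons, the last term is multiplied by 0.80. The third row then becomes 0.72 + 0.10 × 0.2 × 0.80 = 73.6%, which is close to the 74% above. Under these assumptions the loss runs from 0 to 14 points. The table shows how the mechanism works and is not an estimate for this trial.

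**The case against.** **This may be a detail left to the full protocol or SAP.** The article is a condensed text, the parenthesis defining CTP ischemia may be shorthand, and the exclusion list need not be complete. Prior infarction may already be recorded, since the baseline history is not itemised. This stands in part. The point rests on the definition as printed, which would classify scar as ischemia, and a scar rule elsewhere would settle it.

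**Against the stated target, the case is a legitimate false positive.** The target is FFR-defined ischemia. If a stress-only test cannot separate scar from ischemia in a population with known CAD, counting that limit is fair. This stands. A reader might infer that infarct vessels must be removed from the main estimate. The document does not support that: removal would describe a narrower population, and it would also take out infarct vessels with FFR at or below 0.80 and a CTP defect, which are true positives.

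**The effect could be mistaken for a contrast effect.** A reader might infer that a few infarct territories falling unevenly between arms would distort the iodine comparison. The article states no between-arm test of CTP accuracy. It says that establishing diagnostic validity is not the purpose, and it labels these analyses exploratory. No conclusion about iodine rests on them.

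**A check is already planned for MBF.** The visually nonischemic set should drop most visible scar. This stands, and it limits the MBF part of the point to the vessel-defined set.

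**Conclusion.** The point holds in a limited form. As printed, scar behind a vessel with FFR above 0.80 is scored as a CTP false positive and stays in the vessel-defined MBF sensitivity set. The direction for exploratory specificity and PPV is downward. The size cannot be derived from the document, and it is zero if no FFR-negative vessel in the subset supplies scar. A reader might take the 2 to 14 point loss in the infarct rows of the illustration as a finding about this trial; it follows wholly from assumed inputs.

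The primary HU endpoint, the sample size and the main all-segment MBF analysis are not touched. This is an inexpensive improvement to secondary and exploratory analyses, not a defect in the trial's main inference.

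**What to change.** 1. Record documented prior infarction and its territory from the chart, without reference to the study CT.
2. In the ICA/FFR section and in Statistical methods, keep all vessels in the main CTP-versus-FFR estimate. Add a prespecified sensitivity analysis that excludes vessels supplying a documented infarct, and report sensitivity, specificity, PPV, NPV and AUC both ways.
3. In Image analysis, remove documented infarct territories from the MBF sensitivity set defined by absence of significant stenosis or FFR-defined ischemia. Leave the main all-segment MBF analysis as it is.

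No additional scan or participant is needed. The cost is one more history item, some wording, and somewhat fewer vessels or segments in these secondary sets. Undocumented infarcts will remain, so the second estimate reduces the problem without removing it. Fixing the rule before allocation is linked to the image data also prevents false positives from being excluded after the results are known.

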### Randomization, allocation concealment, and blinding

Participants will be allocated 1:1 to the low- or high-concentration iodine contrast group using a computer-generated allocation protocol prepared by the Department of Preventive Medicine. The allocation sequence will be concealed from the principal investigator, research personnel involved in recruitment and endpoint assessment, participants, image readers, and outcome assessors. The principal investigator and research investigators will not know which contrast concentration is assigned at the time of patient enrollment, image analysis, or endpoint assessment. CT technologists involved in contrast preparation and injection may be aware of the assigned contrast media because the preparations differ; however, they will not participate in patient selection, randomization, image interpretation, endpoint assessment, statistical analysis, or clinical decision-making. After acquisition, CT images will be uploaded to PACS without visible contrast-group identifiers. The principal investigator, research investigators, image readers, and outcome assessors will analyze the anonymized imaging datasets in a blinded arrangement, and the final analytic dataset will be linked to the randomized allocation list only after blinded image analysis is complete. Participants will also not be informed of their assigned contrast concentration. Therefore, the study is described as participant-, investigator-, and reader-blinded, with transparent acknowledgement of technologist unblinding during contrast preparation.

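### The CTP-to-FFR vessel mapping includes an undefined clinical-correlation step with no stated blinding to ICA/FFR, so the exploratory CTP accuracy figures can be overstated

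*Protocol article*

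**What the plan says.** The rule is in the protocol article, Methods, section on exploratory diagnostic performance analyses (ICA and FFR). The index test and its comparator are set out as "CTP ischemia (territorial/segmental defects or low MBF) will be compared with vessel-level FFR where available", and the link between them is made "with mapping of myocardial territories to corresponding coronary vessels using standardized AHA territorial assignments and clinical correlation". The reference standard is fixed per vessel: "FFR ≤ 0.80 will define functionally significant ischemia in the interrogated vessel". Statistical methods then applies to CTP against FFR the same kinds of metric as for CCTA against ICA: sensitivity, specificity, predictive values and ROC/AUC.

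Three other statements bear on the point:

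- **Randomization, allocation concealment, and blinding:** the principal investigator and research investigators "will not know which contrast concentration is assigned at the time of patient enrollment, image analysis, or endpoint assessment". This concerns contrast group; ICA and FFR are not mentioned.
- **Qualitative image quality assessment:** the two radiologists who review the CCTA and CTP datasets are readers "who are blinded to clinical information and contrast-group assignments".
- **Exploratory diagnostic performance analyses:** the caveat given is that "these analyses are subject to potential verification bias and will be interpreted cautiously as prespecified exploratory and hypothesis-generating analyses". No other bias is named there or in Statistical methods.

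The Image analysis section (text after Fig. 3) also plans an MBF sensitivity analysis in "territories not supplied by vessels with significant anatomic stenosis or FFR-defined ischemia", which needs a territory-to-vessel mapping too.

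**The concern.** FFR belongs to a vessel, and a CTP defect belongs to a set of myocardial segments. The mapping decides which segments count for which vessel. For a border segment it therefore decides whether the vessel is scored CTP-positive or CTP-negative.

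A standard AHA assignment makes that decision before any result is known. A clinical-correlation step can change it case by case. By construction, every participant in this analysis has an FFR result, so that result can be part of the clinical picture being correlated. If it is used, the index test is partly built from the reference standard (review or incorporation bias), and agreement tends to be too good.

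The verification-bias caveat does not cover this. Verification bias concerns who goes on to invasive testing. Sensitivity analyses for it would neither detect nor correct a mapping made with the FFR result in view.

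**Working it through.** The plan states no figure that this point depends on, so there is none to reproduce. The check is a reading of the sections against each other, followed by an illustration on assumed values.

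**1. Can the mapping change the score?** Take one CTP defect in a border segment that could belong to an interrogated vessel or to its neighbour.

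| FFR in the interrogated vessel | Segment assigned to that vessel | Segment assigned elsewhere |
|---|---|---|
| ≤ 0.80 | true positive | false negative |
| > 0.80 | false positive | true negative |

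Someone who knows the FFR can pick the concordant cell in either row. Someone who does not know it cannot make the choice depend on the row. Independence therefore turns on whether the mapper can see the FFR.

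**2. Does any stated safeguard keep the FFR from the mapper?**

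- Trial-level blinding is to contrast concentration. It gives no reason to expect the blinded assessors to map differently by arm, but it does not cover the invasive result.
- The radiologists' blinding to clinical information is stated for their image review. The mapping sentence names no actor and no time, so that blinding cannot be carried over to it.
- The caveat and the planned sensitivity analyses concern verification bias only.

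Nothing in the article closes the gap. Elsewhere it does guard against circularity: Image analysis declines to use MBF thresholds to define the main MBF analysis set. The mapping has no comparable guard.

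**3. Which analyses use the mapping?**

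- Primary HU endpoint: no.
- Main MBF analysis: no, since it takes all analyzable segments.
- Exploratory CTP-versus-FFR accuracy: yes.
- MBF sensitivity analysis restricted by anatomic stenosis or FFR: possibly. It needs some mapping, and the article does not say which.

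**4. Illustration only.** Let Se and Sp be the true per-vessel sensitivity and specificity, and m the share of discordant vessels re-matched so as to agree with a known FFR:

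apparent Se = Se + (1 − Se)·m

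apparent Sp = Sp + (1 − Sp)·m

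Se = 0.75, Sp = 0.80 and every value of m are assumptions; none comes from the document.

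| m | Apparent Se | Apparent Sp |
|---|---|---|
| 0 | 0.75 | 0.80 |
| 0.10 | 0.75 + 0.25 × 0.10 = 0.775 | 0.80 + 0.20 × 0.10 = 0.82 |
| 0.20 | 0.75 + 0.25 × 0.20 = 0.80 | 0.80 + 0.20 × 0.20 = 0.84 |
| 0.30 | 0.75 + 0.25 × 0.30 = 0.825 | 0.80 + 0.20 × 0.30 = 0.86 |

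The formula assumes that every re-match creates agreement, so the direction is built in. For a given m it is closer to an upper bound than to an estimate, for two reasons:

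- A vessel with FFR ≤ 0.80 and no defect in a neighbouring territory has nothing to re-match.
- A defect moved off one vessel lands on another. If both were interrogated and both have FFR > 0.80, the move turns one false positive into a true negative and one true negative into a false positive, with no net gain.

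**The case against.** The strongest reply is that the article nowhere says the invasive result will be used. AHA assignment is the named basis, and an ordinary reading of the added step is adjustment for individual coronary supply, such as dominance. Adjustment that correctly reflects anatomy reduces misclassification, and a resulting gain in measured accuracy is not bias. This stands: inflation is a possibility, not something the document shows.

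A reader might also infer that the mapping rule contradicts the radiologists' blinding to clinical information. The document does not support that. The blinding is stated for the image review; the mapping belongs to a different analysis and is assigned to nobody. Both statements hold if someone else does the mapping, or if it is done after the read.

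Nor does the document support the inference that any error must always favour CTP. That follows only if the FFR informs the reassignment and each move creates agreement.

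A further reply is that who maps, when, and from what information belongs in a full protocol or reading manual, which a journal article condenses. The absence of those details alone would indeed be no finding. But the article does state the rule, calls the analyses prespecified, and words the rule so that its second half is open-ended. That wording can be judged as it stands.

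Finally, the analysis is exploratory, and the article says that establishing the diagnostic validity of CCTA or CTP is not its purpose. This limits the severity. It does not make a reported AUC unbiased.

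**Conclusion.** The point holds as a possible bias from an open rule. The mapping of CTP territories to FFR vessels has a discretionary component, and no stated blinding keeps it independent of ICA/FFR. If the invasive result informs the assignment of border segments, the exploratory CTP-versus-FFR sensitivity, specificity, predictive values and AUC can be overstated. If the step uses only dominance or CCTA anatomy, this bias does not arise.

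The size cannot be derived from the document. The illustrative range (sensitivity 0.775 to 0.825 against 0.75, specificity 0.82 to 0.86 against 0.80, for 10% to 30% of discordant vessels re-matched) rests wholly on assumed inputs and should not be cited as an estimate.

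The noninferiority conclusion on HU and the main MBF comparison are unaffected. Low severity; worth changing because the change is cheap and because a mapping made with the FFR in view is hard to undo afterwards.

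**What to change.** In the section on exploratory diagnostic performance analyses, remove the clinical-correlation wording and state the mapping in full:

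- Territories follow the standard AHA assignment, adjusted only for coronary dominance and branch anatomy seen on the participant's own CCTA.
- An existing reader, unaware of the ICA/FFR results and of contrast group, makes the adjustment.
- The mapping is recorded and locked before ICA/FFR data are linked.
- The unadjusted AHA assignment is reported as a sensitivity analysis.
- The same locked mapping is used for the MBF sensitivity analysis that excludes territories by stenosis or FFR.

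The cost is one reworded passage and one locked field on the reading form, with no added participants, procedures or readers. Reported CTP accuracy may come out slightly less favourable.
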